#### Plan to report pre-specified analyses

In our primary outcome paper, we will include results of our pre-specified subgroup analyses. We will name and report all pre-specified subgroups and their rationale for inclusion, the number of post-hoc HTE analyses, and outcomes analyzed. Reporting will include graphical forest plots, with estimated treatment group differences and confidence intervals for all subgroups, as well as tests of treatment-subgroup interactions.

### Mediation analyses

We will perform mediation analyses on the Stage 1 main intervention effects and will follow the literature for development of statistical approaches for mediation analysis of SMART design adaptive interventions. We will test whether the common and specific factors in our causal pathway model significantly mediate the associations of treatment with patient outcomes. Let X be the assigned treatment, Y be 24-week outcomes, and M be the proposed mediator **(**Fig. 6**)**. We will assess mediation using 3 regression equations: 1) *Y* = *c*_1_*X* + *e*_1_, assessing the association of treatment with 24-week outcomes; 2) *M* = *aX* + *e*_2_, assessing the association of treatment with the putative mediator; and 3) *Y* = *c*_2_*X* + *bM* + *e*_3_, associating the association of treatment with 24-week outcome when adjusting for the mediator (termed the “direct effect” of X with Y). Age and sex will be included as covariates in all three equations. We will test whether the estimator of the indirect effect (*a x b*) differs significantly from zero using bias-corrected bootstrapped confidence intervals on the estimator. A significant mediating effect suggests that the association of treatment effects (X) with trial outcomes (Y) in regression (1) is in part explained by treatment effects on mediating outcomes (M) in regression (3).

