Systematic reviews and meta-analyses have consistently shown that pediatric anxiety disorders, like their adult counterparts, are chronic, recurrent, and unstable in their diagnostic classification over time, with new anxiety disorders appearing together with or replacing the initial, primary diagnosis [16, 17], suggesting strongly that clinical trials should consider multiple anxiety disorders and aggregate symptom outcome measures. Systematic reviews and meta-analyses have also documented substantial therapeutic effects for both psychotherapy, particularly CBT (Cognitive Behavioral Therapy) [18, 19], and medication, especially SSRIs (selective serotonin reuptake inhibitors) [20–22]. While response rates to acute treatment near 60% for both CBT [23] and SSRIs [21, 22] may seem encouraging, these rates also mean that approximately 40% fail to respond. Remission rates are lower, 40–50% for both CBT [24] and SSRIs [21, 22], and even poorer in real-world, community settings (20–40%) [25–27]. Long-term follow-up in pediatric studies is rare, but data suggest that outcomes are poor and relapses common, similar to what is observed in adult anxiety disorders, where relapse approaches 60% [16, 28]. Even after gold-standard treatments in the CAMS study (Child/Adolescent Anxiety Multimodal Study) – the largest and most rigorous combined medication and CBT trial thus far – 30% were chronic non-responders and an additional 50% relapsed at least once in 4 years, despite receiving post-trial treatment [29]. Racial/ethnic minorities in the CAMS study had significantly lower remission rates in all treatment arms [30]. Long-term outcomes did not vary according to initial treatment with CBT, medication, or their combination. Predictors of poor acute treatment outcomes include more severe symptoms, more functional impairment [29, 31], low socioeconomic status (SES) [32], and a primary diagnosis of social phobia [31, 32]. More residual symptoms and functional impairment following acute treatment predict relapse, suggesting that treatment should aim to achieve remission from all anxiety disorders, and with as few residual symptoms of any kind of anxiety as possible [29]. These predictors of relapse have informed our requirements for, and definition of, clinical remission during this trial.

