Exposure also promotes the development of cognitive, emotion regulation, and behavioral skills for coping more effectively with fear, termed *coping efficacy.* Coping efficacy diminishes the conditioned fear response and provides the opportunity for new extinction learning, with an attendant inhibition of maladaptive avoidance. Practicing these skills in different fear-inducing contexts supports generalization of inhibitory learning and stronger extinction of fear responses [78]. Of note, both time spent in exposure tasks, and level of difficulty of the exposures tolerated, predicted better outcomes to *Coping Cat* within the CAMS sample [119]. These findings directly informed our decision to have additional exposure practice and mastery be the focus of our Phase 2 CBT optimization protocol. In addition, efficacy measures in the CAMS trial outperformed specific measures of cognitive change in mediational models on Coping Cat effects, suggesting that development of coping efficacy may mediate CBT outcomes [120].

We will obtain after each CBT session a therapist-rated measure of 3 key facets of exposure practice (quantity, difficulty level, and mastery of exposure tasks) [119], which we will use to craft an index of tolerance to exposure – a CBT-specific factor in effecting patient outcomes. As a complement to this in-session measure of tolerance of exposure, we will also obtain at baseline and then every fourth session the parent version of the 8-item *Child Anxiety Avoidance Scales* [110], a measure of the evolving real-world CBT skill set outside of session that assesses the reduction of anxious avoidance when presented with threatening stimuli. Finally, we will use our measure of Self-efficacy from the NIH toolbox measure of Life-Satistfaction as a proxy for coping efficacy to test this CBT-specfic pathway. We expect that measures of each of the common factors will independently and positively associate with outcomes in our study for both *Coping Cat* and medication therapies [72, 82, 121], and we expect that the greater therapeutic alliance anticipated with CBT compared with medication therapy will partially mediate differences in clinical outcomes across the two treatment modalities. We also expect that measures of the CBT *specific factors* -- exposure tolerance and coping efficacy -- will positively associate with clinical outcomes in response to *Coping Cat* CBT.

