### Data analysis plans

Upon completion of the final trial participant, we will complete a final database review and finalize data queries, then lock the trial database for final analysis. To evaluate baseline comparability, we will compare demographic and clinical characteristics, and trial outcome measures, at baseline between treatment groups. Continuous baseline measures will be summarized by mean (SD) or median (IQR), and categorical measures by frequency (percent). Standardized group differences will be computed and presented for all baseline variables.

We will conduct an intent-to-treat analysis, by which subjects will be analyzed according to randomized intervention, consistent with standard practice in clinical trials. Distributions of outcome variables will be graphically examined; normalizing transformations will be applied if needed. The 24-week continuous measures of primary and secondary trial outcomes will be compared between treatment groups using general linear models, with the 24-week measure as the dependent variable. SMART design groups will include Stage 1 randomized group and Stage 2 randomized group. The randomization stratification factors (age group,clinical site, and dichotomized baseline parent SCARED-41), as well as baseline measures of the trial outcome (Youth SCARED ratings), will be included as model covariates. Results will be summarized by treatment group means (SDs) and mean treatment group differences (and 95% confidence intervals). No interim analyses are planned.

To **test Main Effect 1**, a 2-group (Stage 1 randomization) analysis of covariance will be used, comparing subjects randomized to medication first to those randomized to CBT first [53, 54, 197]. To **test Main Effect 2** among Stage 1 non-remitters, a 2-group analysis of covariance will also be used, comparing (a) non-remitting subjects randomized at Stage 2 to optimization of their Stage 1 monotherapy, vs (b) non-remitting subjects randomized at Stage 2 to combination treatment (medication+CBT or CBT + medication) across levels of Stage 1 randomization. Finally, to test whether one sequence of treatment modalities (CBT➔CBT; CBT➔med; med➔med; med➔CBT) is significantly better or worse than predicted from the two main effects, an interaction term of Stage 1 randomization with Stage 2 randomization will be added to the model. The addition of the interaction term will allow estimation and testing of each of the 4 treatment sequences [53, 54, 197].

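### The mediation equations adjust only for age and sex; leaving out baseline anxiety severity confounds the mediator–outcome path and can make a null mediator look significant when treatment also shifts that mediator

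*Protocol article*

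**What the plan says.** Under Mediation analyses, the Protocol article defines the variables: "Let X be the assigned treatment, Y be 24-week outcomes, and M be the proposed mediator". Three regressions follow: Y on X, M on X, and Y on X and M together. The covariate rule is "Age and sex will be included as covariates in all three equations", and no other covariate is named. The indirect effect a × b is tested "using bias-corrected bootstrapped confidence intervals on the estimator". The scope is broad: "We will test whether the common and specific factors in our causal pathway model significantly mediate the associations of treatment with patient outcomes". The section also says that the team "will follow the literature for development of statistical approaches for mediation analysis of SMART design adaptive interventions".

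The main model for the same week-24 outcome is richer. Under Data analysis plans, "baseline measures of the trial outcome (Youth SCARED ratings), will be included as model covariates", together with age group, site and dichotomized baseline SCARED.

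Three other statements bear on the point:
- Background: "Predictors of poor acute treatment outcomes include more severe symptoms, more functional impairment".
- Contextualizing factors: baseline anxiety severity is expected to work through the Coping Cat-specific factors.
- Factors specific to Coping Cat CBT: a stronger alliance is anticipated with CBT than with medication. The same section gives the source of the exposure index: "We will obtain after each CBT session a therapist-rated measure of 3 key facets of exposure practice".

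**The concern.** Randomization protects the effect of X on Y (equation 1) and of X on M (equation 2). It does not protect the effect of M on Y in equation 3. Anything that influences both M and Y before treatment starts confounds b unless it is in the model. On the protocol's own account, baseline severity does this for the CBT-specific factors.

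Age and sex do not stand in for severity. The team considers baseline SCARED necessary for the treatment comparison, where randomization already prevents bias, yet omits it from the one equation where its absence causes bias.

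What is at stake is the claim about which ingredients of each treatment work. A biased b also moves the direct effect c2 by the same a × b in the opposite direction. The planned labels of partial or complete, and complementary or suppressive, mediation would inherit the error.

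**Working it through.** **Inputs from the documents.** 404 are randomized with 20% dropout: 404 × 0.8 = 323.2, stated as 324 under Sample size and power. The stated detectable Main Effect 1 of 0.31 SD reproduces: (1.96 + 0.84) × √(4/324) = 0.311. The mediation section gives no figure of its own.

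**Assumptions, not in the documents.** The correlation of baseline severity with M (r_M) is −0.2 to −0.4 and with Y (r_Y) is 0.4 to 0.6. The effect of treatment on M (a) is 0 to 0.8 SD. The confidence level is 95%. M and X have no true effect on Y, so every significant a × b is false.

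**Size of the bias.** With M and Y scaled to unit variance within arm, leaving out severity gives an expected b of r_M × r_Y:
- −0.2 × 0.4 = −0.08
- −0.3 × 0.5 = −0.15
- −0.4 × 0.6 = −0.24

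The standard error of b is about 1/√324 = 0.056. The spurious b is therefore about 1.4, 2.7 and 4.3 standard errors from zero. With a = 0.5 and the middle pair, the spurious indirect effect is 0.5 × (−0.15) = −0.075 SD.

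**Simulation of the stated test.** Each setting used 600 trials of n = 324 with 500 bootstrap resamples. Equations 2 and 3 included age and sex, and a × b was tested with a bias-corrected bootstrap interval. Entries are false-positive rates with age and sex only, then with baseline severity added.

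| a (SD) | r_M = 0, r_Y = 0.5 | −0.2, 0.4 | −0.3, 0.5 | −0.4, 0.6 |
|---|---|---|---|---|
| 0 | 0.8% / 0.7% | 2.8% / 0.7% | 9.2% / 1.3% | 7.0% / 0.7% |
| 0.3 | 6.3% / 7.2% | 32.0% / 7.2% | 66.8% / 7.8% | 80.8% / 6.7% |
| 0.5 | 7.0% / 6.2% | 34.2% / 6.7% | 81.3% / 6.7% | 99.2% / 8.5% |
| 0.8 | 6.3% / 8.2% | 37.7% / 6.3% | 79.0% / 6.3% | 99.8% / 5.0% |

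The mean simulated b (−0.08, −0.15, −0.24) agrees with the formula. The bootstrap test itself runs slightly above 5%, so 6% to 8% is the practical baseline once a is not zero. The Monte Carlo standard error is about 1 percentage point near 7% and at most 2 points elsewhere.

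**Re-randomization.** Separate runs had no baseline confounding but did re-randomize non-remitters. With M measured in Stage 1, the false-positive rate was 7.0% (a = 0.3) and 7.3% (a = 0.5), which is the method's own baseline. One run with M measured after Stage 2 (a = 0.3) gave 7.3%. That run reassures less. It assumed that the added modality raises M by 0.5 SD and lowers Y by 0.4 SD, with half of week-12 symptoms carried into Y. The resulting covariance of M and Y is 0.5 × (0.5 × 0.193 − 0.4 × 0.21) = 0.006, a near-cancellation. Here 0.193 is the covariance of receiving the added modality with week-12 symptoms, and 0.21 = 0.3 × 0.7 is its variance.

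**Exposure index.** It is rated after CBT sessions only. No fluoxetine-first participant has it in Stage 1. At 40% remission, 0.6 × 0.5 = 30% of that arm (202 × 0.3, about 61) would have CBT in Stage 2, so about 70% never have it during the trial. Equation 2 cannot be fitted meaningfully for it.

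**The case against.** Mediation is not among the Specific Aims, the article condenses a fuller plan, and the section promises to follow the literature on SMART mediation and to fit a later multi-mediator model. This lowers the importance of the point but does not answer it. The covariates are stated, not left open, and neither promise names baseline severity. The sensitivity analysis with extra covariates is triggered by imbalance between arms, which has no bearing on confounding of M with Y.

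A second objection is that the documents do not put both conditions on one mediator in so many words. The severity link is stated for the CBT-specific factors, and the expected treatment difference for alliance. This stands in part. The CBT-specific factors are described as unique to CBT, which implies a treatment difference. For alliance the severity link is less direct: the protocol cites evidence that better outcomes predict a better alliance.

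A reader might infer three stronger things that the documents and calculations do not support:
- **That baseline severity alone creates false mediators.** Treatment must also shift M. With a = 0 the unadjusted rate was 3% to 9%.
- **That a week-24 outcome after re-randomization is itself an error.** Week 24 is the horizon of Aim (a) and of Main Effect 1, so it is a choice of estimand. Stage 2 is randomized, and with M taken in Stage 1 no inflation appeared. Moving Y to week 12 would make M and Y simultaneous for self-efficacy, which Table 2 schedules at baseline, weeks 12 and 24, and quarterly.
- **That no CBT-specific mediator can be compared between arms.** The avoidance and self-efficacy measures are not restricted to one arm in Table 2. The mediation section does not name the exposure index as M; it only fails to exclude it.

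**Conclusion.** The point holds for the covariate set. As written, the mediation equations leave the mediator–outcome path confounded by baseline severity. Under the assumed correlations and a treatment effect on M of 0.3 to 0.8 SD, a null mediator is declared significant in roughly 32% to 99% of trials, against about 5% to 9% with baseline severity included. The range is wide because it depends on correlations that the documents do not give. If severity is unrelated to M, the rate is 6% to 7% without any adjustment. The direction and mechanism do not depend on the exact values.

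The narrower point on the exposure index also holds: it cannot serve as a between-arm mediator. The primary and secondary treatment comparisons are not touched.

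**What to change.** - Add the baseline value of the outcome, the baseline value of the mediator where collected, and the stratification factors to all three equations, alongside age and sex.
- Keep Y at week 24. State that M is measured at or before week 12, so that it precedes both Y and Stage 2 re-randomization.
- Analyse the therapist-rated exposure index within CBT recipients, as an association with outcome and not as a mediator of the arm difference.

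The cost is wording only. Table 2 already schedules baseline SCARED, alliance, avoidance and self-efficacy, and week-12 or earlier values of each mediator. One limit should be acknowledged in reporting: baseline adjustment does not remove confounding by symptom change that arises after randomization but before M is measured, so b remains an observational estimate.

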### Study design

This will be a single-blind [126, 127] SMART design [51, 52] of 24-week treatment duration that will employ two sequential levels of randomization, one in each of two 12-week stages of the study **(**Fig. 2**)**.

#### Stage 1

404 children ages 8–17 who have an anxiety disorder will be randomized 1:1 to receive 12 weeks of either the medication fluoxetine in upward-titrated dosages or weekly CBT implemented using the *Coping Cat* CBT model [128].

#### Stage 2

All participants who do not remit in Stage 1 will be randomized 1:1 to either (1) optimization of their Stage 1 treatment, or (2) optimization of their Stage 1 treatment and addition of the other treatment modality (Fig. 2). Study assessments will be obtained at baseline, week 12, and week 24. A small subset of measures (SCARED-41, and the Pediatric Side Effect Questionnaire) will also be obtained at weeks 6 and 18. Participants who remit during the first 12 weeks of treatment will continue maintenance-level therapy with the single-modality treatment received in Stage 1. If a participant who achieved clinical remission during the first 12 weeks of treatment relapses at the week 18 study assessment (defined as having a SCARED total score of ≥25), the participant will be referred to the treating clinician to restart or slightly intensify the previous treatment assigned in Stage 1 of the study. Following conclusion of the 24-week trial, we will follow and obtain all the same study assessments in all participants quarterly for at least 12 months [44, 126, 127].

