(3) Group main effect ESs were then computed for a Stage 1 remission rate of 40%. Our estimated Stage 1 remission rate of 40% is a conservative estimate based on the CAMS remission rate of 35% achieved for ethnic minorities, when applying remission criteria less stringent than ours [30]. In CAMS, the 12-week remission rate was also approximately 10% higher in medication-only compared to CBT-only. We used this 10% difference in these calculations to compute ESs and resulting sample size estimates. For Main Effect 1 (start with medication vs start with CBT), ESs for all 3 medication or CBT groups (1: remitter; 2: non-remitter➔optimize monotherapy; 3: non-remitter➔medication+CBT) were computed as a weighted average of the group-specific ESs. Weights were the remission rate, with the non-remitter weight (1 minus remission-rate) split equally among the 2 randomized non-remitter groups (reflecting 1:1 Stage 2 randomization among non-remitters). For Main Effect 2 (among Stage 1 non-remitters, optimize Stage 1 treatment vs add the other treatment), ESs were computed as a weighted average of the ESs for monotherapy optimizers (medication+, CBT+) and a weighted average of the combined (medication+CBT, CBT + medication) groups. These weights were again 0.5*(1- remission-rate).

[4] We then computed the sample size required to detect Main Effect 2 (optimize monotherapy vs add the other therapy in non-remitters) at 80% power and tested at a 2-sided alpha = 0.05. From our computations above, the Main Effect 2 ES was approximately 0.40 SD, requiring a sample size of 194 participants among Stage 1 non-remitters. Increasing the sample size of 194 by the non-remission rate (N divided by non-remission rate) and by the estimated 20% dropout rate, yielded a sample size of 404 (202 per group) for Stage 1 remission rates of 40%. Randomizing 404 participants, with an estimated 324 finishing the trial and a remission rate of 40%, will provide the ability to detect an overall Main Effect 1 (medication first versus CBT first) ES of ≥0.31 SD with 80% power.

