#### Multiplicity

The primary outcome (Youth SCARED) will be tested at an α = 0.05. Evaluation of secondary, exploratory, and all subgroup analyses will control for the false discovery rate [200].

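### The bias-corrected bootstrap test of mediation rejects a true null up to about 8% of the time at this sample size when only one path is zero

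*Protocol article*

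**What the plan says.** The Mediation analyses section of the protocol article sets up three regressions: outcome on treatment, mediator on treatment (path a), and outcome on treatment and mediator (path b). The exposure is the first randomisation: "We will perform mediation analyses on the Stage 1 main intervention effects". On adjustment it says "Age and sex will be included as covariates in all three equations". The decision rule reads "We will test whether the estimator of the indirect effect" a x b differs significantly from zero, "using bias-corrected bootstrapped confidence intervals on the estimator". The section gives no interval level, number of resamples or error rate for this test.

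The Multiplicity section says "Evaluation of secondary, exploratory, and all subgroup analyses will control for the false discovery rate". It does not name mediation, and the Mediation analyses section does not label itself secondary or exploratory.

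**The concern.** The indirect effect is zero whenever either path is zero, so the null has three forms: both paths zero, only a zero, or only b zero. When only one is zero, the bias correction shifts the interval limits in a way that makes the interval exclude zero more often than its nominal level allows.

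The one-path null is a realistic case in this trial. The section on factors specific to Coping Cat CBT anticipates a stronger therapeutic alliance under CBT than under medication, so a is expected to be non-zero. Whether alliance then drives the outcome (b) is the open question. The same section expects the common factors to be associated with outcome in both modalities, so b could be non-zero for a factor that does not differ between arms.

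Several candidate mediators are to be examined, and the plan goes on to label mediation as partial or complete and as complementary or suppressive. A false rejection would therefore be carried into a statement about how the treatments work.

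**Working it through.** **Inputs from the protocol article**
- Allocation, Study design section: "404 children ages 8–17 who have an anxiety disorder will be randomized 1:1".
- Analysed sample, Sample size and power section: 324 expected completers.
- Test level: none is stated for mediation. The sample-size calculation was made "at 80% power and tested at a 2-sided alpha = 0.05", so a 95% interval is assumed here.
- Paths a and b: not given, so a range is shown.

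**The plan's own sample size.** 194 non-remitters / 0.6 / 0.8 = 404.2, matching 404. Retaining 80% gives 404 x 0.8 = 323.2, against the 324 used. With 162 per arm, the detectable difference is (1.960 + 0.842) x sqrt(2/162) = 0.311 SD, matching the stated 0.31. So 324 is the right size for the check.

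**Simulation model.** M = aX + e and Y = bM + e', with X balanced and binary, unit-variance normal errors and no direct effect. The fitted models are M on X, age and sex, and Y on X, M, age and sex. Age and sex were generated without effects.

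**Three tests on the same datasets**
- Bias-corrected: z0 = Φ⁻¹(share of bootstrap a x b values below the estimate). The limits are the bootstrap quantiles at Φ(2·z0 ± 1.96). Reject if the interval excludes zero.
- Percentile: the 2.5% and 97.5% bootstrap quantiles.
- Joint significance: reject if a and b are each significant at 5%, which means that the larger of their two p-values is below 0.05.

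Each row below uses 10,000 datasets with 1,000 or 2,000 resamples. The Monte Carlo standard error near 8% is sqrt(0.08 x 0.92 / 10,000) = 0.27 percentage points.

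**False-positive rate at n = 324 (a x b = 0 in every row)**

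| a (SD) | b | Bias-corrected | Percentile | Joint |
|---|---|---|---|---|
| 0 | 0 | 0.5% | 0.2% | 0.2% |
| 0 | 0.10 | 4.0% | 1.5% | 1.9% |
| 0 | 0.14 | 6.1% | 3.2% | 3.5% |
| 0 | 0.20 | 7.6% | 4.6% | 4.7% |
| 0 | 0.25 | 7.5% | 5.3% | 5.1% |
| 0 | 0.30 | 7.0% | 5.3% | 5.0% |
| 0 | 0.59 | 5.2% | 4.9% | 4.7% |
| 0.20 | 0 | 3.7% | 1.7% | 1.9% |
| 0.30 | 0 | 7.1% | 4.0% | 4.2% |
| 0.40 | 0 | 7.9% | 4.9% | 4.8% |
| 0.45 | 0 | 7.9% | 5.4% | 5.2% |
| 0.50 | 0 | 7.1% | 5.1% | 4.8% |
| 0.80 | 0 | 6.4% | 5.5% | 4.9% |

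**Other sample sizes.** The bias-corrected peak is 7.7% at n = 404 (6,000 datasets per row) and 8.2% at n = 194 (16,000 per row). At n = 404 the highest percentile and joint rates are 5.9% and 5.6%, with a standard error of about 0.3 points.

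**Repeat without covariates.** With 8,000 datasets at n = 324, the bias-corrected test gave 7.8% (a = 0.4, b = 0), 7.2% (a = 0, b = 0.2) and 7.0% (a = 0.31, b = 0). The percentile interval gave 4.7%, 4.6% and 3.7%. The joint test gave 4.5%, 4.4% and 4.1%.

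**Power.** At a = 0.31, b = 0.14, the bias-corrected test rejects in about 67% of datasets, and the two alternatives in 55–58%.

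**The case against.** The strongest reply is that the excess is modest, conditional and confined to a supporting analysis. It is about 3 percentage points at worst, and it disappears when the non-zero path is very small, when b is large, or when both paths are zero. The protocol gives no a or b, so nobody can say which row of the table applies. Mediation is not among the numbered aims or hypotheses. A joint multiple-mediator model is the planned last step, and the plan also undertakes to follow the literature on mediation methods for SMART designs. For exploratory mechanism work, giving up roughly 10 points of power to remove 3 points of worst-case error is partly a matter of judgement.

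Much of this stands, and it limits the weight of the point. It does not remove it. The bias-corrected interval is the only test that the section names, and the deference to the literature names no other. The range with excess error includes cases that the protocol's own expectations make plausible. Part of the power advantage comes from rejecting too often.

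Two stronger readings are tempting and should be resisted. A reader might infer that an interval-only rule cannot supply a p-value for false-discovery control. It can, by finding the confidence level at which the limit touches zero, although that p-value carries the same inflation. Since the Multiplicity section does not name mediation, how it enters that control may be settled in an analysis plan not shown here. A reader might also compound the rate over many mediators into a large chance of at least one false mechanism. That would need a mediator count that the protocol does not state, independence between mediators that the plan itself expects to be correlated, every mediator near the peak rate, and no false-discovery control.

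**Conclusion.** The point holds in a limited form. As written, the test of the indirect effect has a worst-case false-positive rate of about 8% at n = 324, against a conventional 5%: roughly one false rejection in 13 instead of one in 20. This occurs only when one path is null and the other is small to moderate. A rate as high as 9% was not reached at any of the sample sizes examined.

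The result assumes a 95% interval, normal errors, complete cases, one mediator at a time and no direct effect. The primary and secondary comparisons of treatments do not use this test and are unaffected. The correction is worth making before data are seen because it is nearly free, but it concerns only the mechanism analyses.

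**What to change.** In the Mediation analyses section, replace the bias-corrected interval with the percentile bootstrap interval, state its level, and make it the single deciding rule for each indirect effect. If mediation is to come under false-discovery control, use one p-value-based rule in its place: the joint-significance test, taking the larger of the p-values for a and b. Do not run both rules as deciders, because they can disagree for the same mediator.

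The cost is one software option and a sentence in the plan, plus the fall in apparent power shown in the working.
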